## Abstract

**Background:**

The gut-brain axis is a bidirectional signaling pathway between the gastrointestinal tract and the brain; it is being studied because of its potential influence in mediating mood, anxiety, and other neuropsychiatric symptoms. Previous research examining the effects of gut microbiota on neuropsychiatric disorders suggests that gut repopulation treatments such as probiotics, microbe therapy, and fecal microbiota transplantation show promising results in treating symptoms of anxiety and depression. This study explores the use of an alternative gut repopulation treatment to fecal microbiota transplantation, known as Microbial Ecosystem Therapeutic (MET)-2, as an intervention against symptoms of depression. MET-2 is a daily, orally administered capsule containing 40 bacterial strains purified from a single healthy donor.

**Objective:**

The primary aim of this study is to assess changes in mood in people with major depression that occur pre-, post-, and during the administration of MET-2. The secondary aims are to assess changes in anxiety symptoms, blood biomarker concentrations, and the level of repopulation of healthy gut bacteria as a response to treatment.

**Methods:**

In this study, we will recruit 60 adults aged between 18 and 45 years old with major depression and randomly assign them to treatment or placebo groups. Patients in the treatment group will receive MET-2 once a day for 6 weeks, whereas patients in the placebo group will receive a matching placebo for 6 weeks. Participants will complete biweekly visits during the treatment period and a follow-up visit at 2 weeks post treatment. As a primary outcome measure, participants’ mood will be assessed using the Montgomery-Asberg Depression Rating Scale. Secondary outcome measures include changes in mood, anxiety, early stress, gastrointestinal symptoms, and tolerability of MET-2 treatment using a series of clinical scales and changes in blood markers, particularly immunoglobulins (Igs; IgA, IgG, and IgM) and inflammatory markers (C-reactive protein, tumor necrosis factor-α, transforming growth factor-β, interleukin-6, and interleukin-10). Changes in the relative abundance, diversity, and level of engraftment in fecal samples will be assessed using 16S rRNA sequencing. All data will be integrated to identify biomarkers that could indicate disease state or predict improvement in depressive symptoms in response to MET-2 treatment.

**Results:**

Given the association between the gut microbiome and depression, we hypothesized that participants receiving MET-2 would experience greater improvement in depressive symptoms than those receiving placebo owing to the recolonization of the gut microbiome with healthy bacteria modulating the gut-brain axis connection.

**Conclusions:**

This study is the first of its kind to evaluate the safety and efficacy of a microbial therapy such as MET-2 in comparison with placebo for major depressive disorder. We hope that this study will also reveal the potential capabilities of microbial therapies to treat other psychiatric illnesses and mood disorders.

**Trial Registration:**

ClinicalTrials.gov NCT04602715; https://clinicaltrials.gov/ct2/show/NCT04602715

**International Registered Report Identifier (IRRID):**

DERR1-10.2196/31439

## Introduction

### Background

Research efforts to identify the pathophysiology and underlying mechanisms of psychiatric illnesses, such as major depressive disorder (MDD), are on the rise owing to the staggering economic burden and prevalence of mental illness. In Canada, mental illness affects approximately 20% of people and costs the Canadian economy more than Can $51 (US $39.48) billion a year, of which MDD is a major contributor [1,2]. MDD is a highly prevalent and debilitating psychiatric disorder characterized by a persistent depressed mood and loss of interest or pleasure in the surroundings. Common symptoms of MDD can include but are not limited to depressed mood, anhedonia, changes in appetite, trouble sleeping, reduced energy and fatigue, feelings of worthlessness, guilt, hopelessness, and thoughts of death or suicide [3].

Although there are a variety of psychological, pharmacological, and neurostimulation treatment methods available for people with MDD, such as cognitive behavioral therapy, antidepressant medications, and electroconvulsive therapy for treatment-resistant cases [4-6], finding the optimal treatment method can be challenging owing to a high level of individual variability among patients. Variables such as environmental influences, stress, and genetics play a role in determining the severity and course of symptoms and the response to treatment [7-9]. Furthermore, emerging treatment options addressing individual variability in patients with MDD have demonstrated the potential for creating a more precise and personalized approach to treatment, specifically within psychiatry [10].

### Rationale for the Study

#### Composition of the Gut Microbiome

The colonization of bacteria in the gut begins at birth and significantly influences gut health throughout the lifespan [11]. In adults, the gut microbiome comprises more than 100 trillion commensal bacteria essential for the normal development and regulation of the immune system, central nervous system circuitry, and gastrointestinal (GI) functioning [12]. Under certain circumstances, environmental risk factors such as diet, lifestyle, stress, medications, and genetics can alter microbiota composition and deviate the homeostatic balance within the microbiome [13].

Previous studies have demonstrated that these alterations in microbiota composition owing to external factors may be mediated by the gut-brain axis (GBA). The GBA is a bidirectional, biochemical, and neural signaling pathway between the GI tract and the brain [14]. Although it has been long established that there is communication between the brain and the gut, only recently has there been a surge of interest in the GBA for its potential influence on depression and other symptoms of psychiatric illnesses [12]. Owing to the interaction between the gut and environmental risk factors of anxiety and depression, some interventions target the gut microbiome to aid in alleviating symptoms of anxiety and depression [15].

#### Gut Microbiota and Psychiatric Symptoms

Although alterations of gut microbiota may play a role in the etiology of psychiatric illnesses, the pathophysiology of MDD and how the GBA directly affects mood is complex. One of the most well-known hypotheses for the pathophysiology of depression is the monoamine hypothesis. It predicts that a deficiency in the levels of dopamine, serotonin, and norepinephrine in the central nervous system may be a key factor in the underlying mechanisms of depression [16]. Other central mechanisms that are also hypothesized to be involved in the pathophysiology of MDD include inflammation of the immune system and microbial imbalance [7].

Several studies have documented that patients diagnosed with MDD often present with elevated levels of proinflammatory cytokines, such as interleukin-6, and decreased levels of anti-inflammatory cytokines, such as interleukin-10 [7,17,18]. This proinflammatory state observed in patients with depression reaffirms the neuroinflammation hypothesis, which suggests that an increase in systemic inflammation is likely to be involved in the pathophysiology of depression by decreasing the synthesis and production of monoamines such as serotonin, resulting in a reduction of serotonin and an increase in depressive behavior [19].

Recent literature documenting the relationship between gut microbiota and symptoms of psychiatric illness has uncovered interesting findings. Microbial balance in the gut is an integral part of gut health; however, when one experiences an imbalance, the integrity of the protective epithelial and mucosal gut barrier can be compromised. This compromise might result in increased intestinal permeability of the GI tract, referred to as *leaky gut*. Leaky gut has been associated with various conditions, such as irritable bowel syndrome, autoimmune disorders, and multiple psychiatric illnesses [15]. Maes et al [20] demonstrated that bacterial translocation from the gut, also known as leaky gut, could activate immune cells to evoke specific IgA and IgM responses. Interestingly, patients diagnosed with depression often exhibit the same elevated levels of IgA and IgM responses, which may be owing to the progressive amplification of the immune pathways and overall increased systematic inflammation [20].

Despite these relevant advances in recent literature, a complete understanding of microbial changes in the gut and their associated outcomes is still required. Previous studies have demonstrated that patients diagnosed with depression often display altered gut microbiota composition compared with healthy controls [12,21,22], which may result from the decreased abundance and lack of diversity among healthy gut microbiota [21]. In an attempt to address this problem, related research has turned to fecal microbiota transplantation (FMT) as a potential treatment option to improve symptoms of depression. FMT is a therapeutic approach that aims to repopulate the gut of an individual with fecal bacteria from a healthy donor via colonoscopy, nasogastric tube, or oral administration [23,24]. A potential advantage of discovering this link between symptoms of depression and microbiota in the gut is the greater accessibility and modifiability of microbiota compared with the human genome, giving microbial therapies a greater opportunity for aiding in the personalization of treatments for psychiatric illnesses [25]. Furthermore, given the adaptable nature of the microbiome, it may be a good representation of the individual’s history and could better explain the differences in the risk of illness, disease course, and response to treatment.

### Microbial Ecosystem Therapeutics

Microbial Ecosystem Therapeutic (MET)-2 is an oral, daily administered, novel treatment approach designed to repopulate the gut with microbiota from a healthy donor. MET-2 is a defined microbial community comprised 40 strains of lyophilized bacteria that are lab-grown and purified from a healthy 25-year-old donor’s stool. MET-2 was originally developed by researchers at Queen’s University and the University of Guelph to treat symptoms of early depression and help restore the normal gut flora. The original mixture contained pure cultures of intestinal bacteria, referred to as *Repoopulate* or MET-1, which was composed of 33 strains of bacteria that were chosen for their favorable safety profile [26]. This mixture was then refined, modified, and improved to 40 strains to create MET-2. Capsules were chosen instead of traditional FMT not only to increase acceptability to participants but also to allow for easier administration of the product for consecutive days rather than the use of raw fecal material administered via rectal suspension.

This study aims to evaluate the effects of MET-2 on symptoms of depression using pre- and posttreatment scores for overall depression and specific depressive symptoms. Our primary aim is to demonstrate the efficacy of MET-2 treatment, in comparison with placebo, on mood and related symptoms in participants with depression, using the Montgomery-Asberg Depression Rating Scale (MADRS) [27]. Those with at least a 50% reduction in MADRS scores will be considered successful responders to treatment. The secondary aims are to assess changes in anxiety symptoms, immune marker levels in response to MET-2 treatment, and the safety and tolerability of MET-2 treatment, and to evaluate any potential correlations between early life stress (eg, childhood emotional, physical, or sexual abuse history) and response to MET-2 treatment.

## Methods

### Study Design

This study is a phase 2, randomized, double-blinded, placebo-controlled clinical trial exploring the efficacy of MET‑2 as a treatment for depressive symptoms in participants with MDD. We will randomize 60 participants with MDD into two arms: the treatment arm (30/60, 50%) and the placebo arm (30/60, 50%). Participants will consume either the investigational product MET-2 or a matching placebo daily for 6 weeks.

### Setting

This study will occur at 3 sites: the Providence Care Hospital, Kingston, Ontario, Canada; the Centre for Addiction and Mental Health, Toronto, Ontario, Canada; and the University of Minnesota Medical School, Minneapolis, Minnesota, United States. There will be a total of 6 visits: a screening visit, a baseline visit (week 0), 3 treatment-period visits (weeks 2, 4, and 6), and a 2-week follow-up visit as outlined in the schedule of assessments (Table S1 in Multimedia Appendix 1).

### Participants and Recruitment

This study will recruit 60 eligible participants aged between 18 and 45 years from the Kingston and Greater Toronto areas in Ontario, Canada, and the Minneapolis area in Minnesota, United States, using clinical referrals and web-based and paper advertisements. Web-based advertisements will be posted on social media platforms, whereas posters will be placed around university and college campuses, on community bulletin boards, clinics, and counseling centers. At the screening visit, all participants will be informed of the study, and any questions and concerns they may have will be addressed. Once consent is obtained, participants will then be thoroughly screened using inclusion and exclusion criteria (Textbox S1 in Multimedia Appendix 1) to ensure they are eligible for the study. Participants will be screened using the Mini-International Neuropsychiatric Interview to confirm the diagnosis of MDD and required a minimum MADRS score of ≥15 to be considered for inclusion in the trial.

### Treatment

#### Study Drug

The 0.5-g MET-2 and placebo will be supplied as capsules for oral administration. Placebo capsules will be filled with cellulose and will be identical in appearance. The participants will be provided with a 4-week supply of either MET-2 or placebo capsules at the baseline visit and a 2-week supply at the week 4 visit. Loading or booster doses will be kept separate from daily maintenance doses.

The 0.5-g MET-2 capsules are produced under conditions compatible with good manufacturing practices at the University of Guelph and are shipped at room temperature and sealed under anaerobic conditions. All capsules are to be stored at room temperature.

#### Administration of Study Drug

Participants who meet the inclusion criteria and pass screening will be scheduled to start treatment at baseline. At the baseline visit, all participants will receive a 10-capsule orally administered loading dose of 5 g of either MET-2 or placebo on both days 1 and 2 (Table S2 in Multimedia Appendix 1). The participant will consume the initial loading dose in the clinic and receive the second loading dose to be taken at home on day 2. The participant will also remain at the clinic for 30 minutes after receiving the first loading dose to ensure there are no adverse reactions to the medication. A 3-capsule maintenance dose containing 1.5 g of MET-2 or placebo will be administered for the remainder of the 2-week interval from 3 to 14 days. At the week 2 visit, participants will be asked to take a 10-capsule booster dose on days 15 and 16. The 3-capsule maintenance dose will be administered for the remainder of the study for a total of 6 weeks of treatment.

If a participant is a nonresponder (a participant whose MADRS total score is not reduced by at least 50% from baseline by week 4 visit), an additional 10-capsule booster dose is to be administered at week 4 for 2 days (days 29 and 30) followed by a maintenance dose of 3 capsules for the remainder of the study (Table S2 in Multimedia Appendix 1). Responders (participants whose MADRS score is reduced by ≥50%) will not receive a booster dose at week 4. Participants will not take the maintenance dose during the loading or booster dose periods.

#### Treatment Compliance

Compliance with treatment will be assessed by reviewing the participant’s personal logs and charts while documenting any missed and unused treatment material during the 6 weeks of intervention.

### Efficacy Endpoints

#### Primary Efficacy Endpoint

At the first endpoint, we will assess changes in symptoms of depression from baseline to week 6 as measured by MADRS scores.

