#### Secondary Endpoints

The secondary endpoints are:

Changes in symptoms of depression from baseline to week 8 as measured by the Clinical Global Impressions (CGI), Snaith-Hamilton pleasure scale (SHAPS), and Quick Inventory of Depressive Symptomatology (QIDS)-SR16 scores.Changes in symptoms of anxiety from baseline to week 8 as measured by the generalized anxiety disorder (GAD)-7 and Hamilton anxiety rating scale (HAM-A) scores.Changes in immune marker concentrations from screening to week 4 and week 8.Changes in symptoms of depression and anxiety from baseline to week 2, week 4, week 6, and the 2-week follow-up measured using the MADRS, HAM-A, and GAD-7 scores.Changes in relative abundance, diversity, and level of engraftment in stool samples, as measured by 16S rRNA sequencing.

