### Statistics

#### Sample Size Determination

The sample size for this clinical investigation was calculated based on the results from the pilot study and the change from baseline to week 8 of the first 13 participants for the MADRS (primary endpoint) and GAD-7 scores (first secondary endpoint). The change from baseline to week 8 was used for the two endpoints, mirroring the time frame for the evaluation of the primary and first secondary endpoints for this clinical investigation. Two series of estimates were generated: change from baseline for the participants with scores at baseline and week 8, and a second imputed data set for participants who did not have a week 8 value using the last observation carried forward. Although the final analysis from this study will use multiple imputation to address missing data, using the last recorded observation results in a higher SD and is considered a reasonable approach to derive a range of estimates. Estimates from the pilot investigation are presented in Table S4 in Multimedia Appendix 1.

For estimation purposes, it is assumed that the placebo participants will have a response that is 50% of the active treatment group, and the SD will be the same between the two treatment groups. The randomization will be in a 1:1 ratio (active:placebo), and the type 1 error rate will be 5%. The resulting sample sizes for 80%, 85%, and 90% power are presented in Table S5 in Multimedia Appendix 1.

If the true mean difference between the active and placebo groups is the midpoint between the observed and imputed results, a minimum target sample size of 50 participants will be required for the primary endpoint (MADRS: change at 8 weeks) and 79 participants (GAD-7: change at 8 weeks) for the other endpoints. On the basis of these estimates, the maximum number of participants to be enrolled in this clinical investigation is 80, and the target sample size is 60 participants. An interim assessment will be performed after 30 participants have completed the 8-week evaluation or withdrawn prematurely.

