### Statistical Analysis

The statistical analysis plan will be finalized before database lock and will include a more technical and detailed description of the statistical analyses described in this section. This section summarizes the planned endpoints and statistical analyses. Participants who return after the initial treatment but later withdraw from the study will have their final scores for primary outcomes projected to week 8. If data are missing, the data from the last time point will be projected forward.

Changes from baseline to endpoint in scores on the MADRS, HAM-A, CGI, SHAPS, QIDS-SR16, GAD-7, and Pittsburgh Sleep Quality Index will be analyzed using two-tailed *t* tests or analysis of variance between and within the placebo and active arms. All statistical tests will be performed using the statistical program IBM SPSS with a significance level of .05. Similarly, stool samples will be analyzed for their diversity scores using a paired *t* test and repeated measures analysis of variance. Any changes in diversity scores will then be compared with the clinical scores to determine any correlations.

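### The primary MADRS endpoint is set at week 6 in the endpoint section but at week 8 in the sample-size section, so the stated minimum of 50 is not a calculation for the visit that the endpoint section defines

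*Protocol article*

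**What the plan says.** All references are to the protocol article.

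- **Primary Efficacy Endpoint:** "we will assess changes in symptoms of depression from baseline to week 6 as measured by MADRS scores".
- **Sample Size Determination, basis:** the pilot data used are the "change from baseline to week 8 of the first 13 participants for the MADRS (primary endpoint") and for GAD-7. The choice of week 8 is explained as "mirroring the time frame for the evaluation of the primary and first secondary endpoints for this clinical investigation".
- **Sample Size Determination, result:** "a minimum target sample size of 50 participants will be required for the primary endpoint (MADRS: change at 8 weeks"). The corresponding figure based on GAD-7, also at week 8, is 79. The target is 60 and the maximum 80.
- **Statistical Analysis:** participants who return after initial treatment and later withdraw "will have their final scores for primary outcomes projected to week 8". The same section tests change from baseline to endpoint and names no visit.
- **Secondary Endpoints:** "Changes in symptoms of depression and anxiety from baseline to week 2, week 4, week 6, and the 2-week follow-up measured using the MADRS", together with HAM-A and GAD-7. Both candidate visits for the primary MADRS endpoint are thus also listed as secondary.
- **Study Design:** "Participants will consume either the investigational product MET-2 or a matching placebo daily for 6 weeks". Under Setting, the last visit is a follow-up two weeks after the week-6 visit.

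**The concern.** Week 6 is the end of dosing. Week 8 is two weeks after the last dose. A difference at week 6 is an effect on treatment; a difference at week 8 is an effect that has persisted after stopping. One can be present without the other, so the two visits are not interchangeable readings of one quantity.

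Two things are at stake. First, the primary hypothesis is not uniquely fixed. If the ambiguity lasted until results were known, the more favourable visit could be reported as primary at the .05 level. Second, the sample-size justification belongs to week 8. If the endpoint section governs, the article contains no calculation for its primary endpoint.

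**Working it through.** **1. Does the text itself resolve the conflict?**

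| Section | Time point for the primary MADRS endpoint |
|---|---|
| Primary Efficacy Endpoint | week 6 |
| Sample Size Determination (basis, rationale, result) | week 8 |
| Statistical Analysis, withdrawal rule | scores carried to week 8 |
| Statistical Analysis, tests | no visit named |
| Secondary Endpoints | weeks 6 and 8 both listed as secondary |

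The week-8 pilot data cannot be read as a convenient proxy for week 6, because the sample-size section says that week 8 matches when the primary endpoint is evaluated. The withdrawal rule is weaker evidence: carrying a last score forward to week 8 also fills week 6, so it is compatible with a week-6 analysis. The conflict is between the endpoint section and the sample-size section, and no other section settles it.

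**2. The plan's own figure of 50.**

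Inputs from the article: two-sided alpha 0.05 (5% error rate; two-tailed tests), 1:1 allocation, equal SDs, placebo response half the active response, power of 80%, 85% or 90%. The pilot means and SDs are in Table S4 and the resulting sizes in Table S5, neither of which is shown. The figure of 50 therefore cannot be reproduced forward, and the text does not say which power it belongs to. Solving backwards with n = 25 per arm:

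d = √(2/n) × (1.96 + z_power)

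- 80%: √0.08 × (1.960 + 0.842) = 0.792
- 85%: √0.08 × (1.960 + 1.036) = 0.848
- 90%: √0.08 × (1.960 + 1.282) = 0.917

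These are implied standardised differences at week 8. Nothing in the text carries them to week 6.

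**3. Power with 60 participants if week 6 is primary.**

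Assumption: the week-6 standardised difference is r times the week-8 value. With 30 per arm,

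power = Φ(r × d × √15 − 1.96).

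Example for the 80% row at r = 0.8: 0.634 × 3.873 − 1.960 = 0.495, and Φ(0.495) = 0.69. The required total scales as 50/r², rounded up to equal arms.

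| r | Total needed | Power at 60 if 50 is the 80% figure | Power at 60 if 50 is the 90% figure |
|---|---|---|---|
| 0.8 | 80 | 69% | 81% |
| 0.9 | 62 | 79% | 89% |
| 1.0 | 50 | 87% | 94% |
| 1.1 | 42 | 92% | 97% |
| 1.2 | 36 | 96% | 99% |

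**4. Type I error if the visit is chosen after the results.**

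With Z6 and Z8 standard bivariate normal under the null with correlation ρ (assumed), P(|Z6| > 1.96 or |Z8| > 1.96) is:

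- ρ = 0.7: 0.0835
- ρ = 0.8: 0.0781
- ρ = 0.9: 0.0704

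That is about 7.0% to 8.3%, against a nominal 5%.

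**The case against.** The strongest reply is that the section headed as the primary endpoint names exactly one, at week 6, and no co-primary is declared. A reader might infer from the mismatch that the trial has two primary endpoints. The article does not support that: it has one endpoint with two stated time points. A reader might also infer that the trial was sized for the wrong visit. That follows only if the endpoint section governs, and the article does not say so. Week 8 also appears in the secondary CGI, SHAPS, QIDS-SR16, GAD-7 and HAM-A endpoints and in the trigger for the interim assessment, so the error could equally lie in the endpoint section.

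It can also be said that the trial is double-blind and that the statistical analysis plan is to be final before database lock, so choosing a visit on the results may never arise. This stands as a limit on the type I figures, which are a worst case. It does not remove the concern, because an interim assessment is planned after 30 participants complete the 8-week evaluation or withdraw, and finalising before lock does not guarantee that the choice is made before that look.

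A third inference, that 60 participants are too few for week 6, is not supported either. The article gives no week-6 mean or SD, and a larger week-6 effect is as open as a smaller one.

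The failure to name a visit in the description of the tests is a detail properly left to the analysis plan, and no criticism is made of it. What remains is a contradiction between two statements that the article does make.

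**Conclusion.** The point holds in this form: the article gives conflicting time points, week 6 and week 8, for its single primary endpoint, and the minimum of 50 was calculated for week 8. This rests on the text alone and needs no assumption.

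The sizes do rest on assumptions. The type I range applies only if the visit is picked after results are seen. The power range depends on the assumed ratio of week-6 to week-8 effect and on which row of the unseen Table S5 yields 50; it runs in both directions, so underpowering is possible but not shown. The contradiction should be corrected before any unblinded data are seen, because it determines which result is the trial's answer.

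**What to change.** Before any unblinded data are seen, including at the interim assessment, state one primary time point and use it throughout: Primary Efficacy Endpoint, Secondary Endpoints, Sample Size Determination and Statistical Analysis. Remove the chosen visit from the secondary MADRS list and keep the other visit there as secondary. Which visit is primary is for the sponsor to decide.

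- **If week 6 is kept:** rebase the sample size on the pilot's week-6 change and SD if they are available, or justify using the week-8 values, and restate the power with 60 participants. Correct the statement that week 8 matches the primary time frame.
- **If week 8 is chosen:** correct the Primary Efficacy Endpoint section; the existing calculation then stands.

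The cost is an amendment to wording and, for week 6, at most one re-run of the sample-size calculation. No visit is added, since both already exist. Whether enrolment is affected depends on the recalculation: for instance, a week-6 effect 10% smaller would need 62 participants, just above the target of 60 and within the maximum of 80.
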